### Statistical analysis

Participants who withdraw during the trial will be invited to return for the follow-up assessments to allow for an intention-to-treat analysis (primary analysis).

#### Sample size calculation

The primary outcome will be the change in PA at follow-up as measured by the pedometer in steps/day. We have shown that a mean difference of 1200 steps between experimental and control groups would have clinical implications [12]. A study sample size of 53 per group was estimated to give 80% power at α = 0.05 to detect a difference of 1200 steps/day between the groups. Given our previous experience with PA interventions in sedentary older adults we have accounted for a potential 25% attrition rate and also adjusted for the intra-class correlation generated by having one mentor with more than one participant. We calculated the inflation factor 1 + r (c-1), in which, on average, each mentor will have 2 participants (c), and we have assumed an intraclass correlation of 0.15 (r), which is considered of medium size with an estimate of 76 participants per group. For the secondary outcome, quality of life this size sample will also allow us to detect a mean difference between groups of 4.5 standardized units, as measured by the SF-36. We also estimate that this would detect an improvement of 20% in the mentoring self-efficacy scale in mentors with 80% of power at α = 0.05.

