#### Data analysis

Continuous variables with normal distribution will be described using means and standard deviations; median and inter-quartile range will be used for those without a normal distribution. Categorical variables will be described using frequency tables. The efficacy of the intervention will be primarily assessed with an intention-to-treat (ITT) analysis at the end of the intervention with secondary analysis for the 12-month time point. This effect will be tested as the interaction between the allocation group (intervention and control) and time, on the primary and secondary outcomes. We will apply multilevel regression models (mixed models) with baseline value of each outcome included in the model as a covariate. In a complementary analysis, we will apply imputation by chained equations to perform an ITT analysis of primary and secondary outcome measures. Alpha will be set at 5% and all statistical tests reported will be two-tailed.

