We will also be able to determine whether this change in PA behavior has an effect on other physical, health and cognitive measures. These findings would be highly significant as it has been estimated that 13% of all cases of Alzheimer’s disease are potentially attributable to physical inactivity and that a 10–25% reduction of physical inactivity would prevent between 380,000 to 1 million AD cases worldwide [76]. Currently there are no effective pharmacological strategies to reduce the risk of cognitive decline and AD, resulting in an increasing call to focus on reducing modifiable risk factors such as midlife hypertension, diabetes mellitus, midlife obesity, depression, smoking, cognitive and physical inactivity. It has been estimated that worldwide about one-third of the AD cases might be attributable to potentially modifiable risk factors [77]. The authors also proposed that with a 10% reduction in each of these risk factors per decade by 2050 there would be a reduction in the prevalence of AD by an estimated 8.3%. Targeted, effective and economically viable PA education and intervention strategies will be needed to achieve these reductions. The current intervention has the potential to be such a program.

Attrition rates for PA interventions in older adults of up to 12 months have ranged from 27% to 50% with most of the attrition occurring in the first 3 months [78]. In a 16-week group-based peer mentor delivered PA intervention 17% attrition was reported at 16 weeks but at 18 months this had increased to 62% [21]. This study demonstrated a significant increase in moderate to vigorous intensity increase in the peer- delivered compared to the community program after 18 months. Our study differs from these earlier studies using peer mentors in that it is home-based, has peer support via telephone and employs a PA focused individualized goal-setting measurement tool and behavior change program. Effective strategies for increasing the PA levels of older adults or indeed preventing the increase in sedentary behavior by active older adults [79] that are cost effective and able to be translated into the community are long overdue [21]. Potentially using the resources within the community that are already health or PA focused such as physically active peer mentors is an attractive approach that will improve the cost effectiveness and make this intervention more translatable into community or clinical settings.

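### The target of 76 per group allows for about 20% attrition, not the stated 25%, so 80% power is not reached on the plan's own assumptions

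*Protocol article*

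**What the plan says.** Everything needed is in the protocol article under Sample size calculation and Data analysis.

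- Starting point: "A study sample size of 53 per group was estimated to give 80% power at α = 0.05 to detect a difference of 1200 steps/day". Tests are two-sided: "Alpha will be set at 5% and all statistical tests reported will be two-tailed".
- Attrition: "we have accounted for a potential 25% attrition rate". The authors base this figure on their own earlier trials in sedentary older adults.
- Clustering: the inflation factor is 1 + r(c − 1), with c = 2 participants per mentor on average.
- Result: "we have assumed an intraclass correlation of 0.15 (r), which is considered of medium size with an estimate of 76 participants per group".

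The attrition step is not written out, and no standard deviation is given. The 80% is attached in words to the 53 per group. That 76 preserves it after both adjustments is implied, since that is the purpose of the inflation.

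**The concern.** If a fraction a of recruits is lost, N recruits leave N(1 − a) for analysis, so the required number must be divided by 1 − a. Multiplying by 1 + a always gives too few, and the gap widens as a grows. The stated 76 is what multiplication gives with the printed inputs.

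What is at stake is how the primary result is read. A null finding on steps per day would be interpreted as coming from a trial that kept 80% power for a 1200-step difference with a quarter of participants lost. On the stated assumptions it would not have done so. There is also little slack to absorb the error: the Discussion reports attrition of 27% to 50% in physical activity interventions of up to 12 months in older adults.

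**Working it through.** **Inputs, all from the protocol article:** 53 per group before inflation, 80% power, two-sided α = 0.05, r = 0.15, c = 2, attrition 25%.

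**Step 1. Clustering factor.** 1 + 0.15 × (2 − 1) = 1.15. Analysable participants needed per group: 53 × 1.15 = 60.95.

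**Step 2. Reproduce the stated figure.**

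| Attrition step | Calculation | Per group |
|---|---|---|
| Multiply by 1 + 0.25 | 60.95 × 1.25 = 76.19 | 76, as stated |
| Divide by 1 − 0.25 | 60.95 / 0.75 = 81.27 | 82 |

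**Step 3. What 76 provides at 25% attrition.** Completers: 76 × 0.75 = 57, about 4 short of 60.95. Attrition that 76 can absorb: 1 − 60.95/76 = 19.8%. Steps 1 to 3 need no standard deviation and do not depend on how the authors arrived at 76.

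**Step 4. Power.** The SD is not stated, so I took the standardised effect implied by 53 per group at 80% power:

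- Normal approximation: (1.960 + 0.842) × √(2/53) = 0.544, an SD of 1200/0.544 ≈ 2205 steps/day.
- t-test: 0.549, an SD of about 2185 steps/day.

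Effective number per group: 57/1.15 = 49.6, against 53. Normal approximation: 0.544 × √(49.6/2) − 1.960 ≈ 0.749, and Φ(0.749) = 77.3%. The t-test calculation also gives 77.3%.

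**Step 5. Check of the proposed number.** 82 per group: 82 × 0.75 = 61.5 completers, 61.5/1.15 = 53.5 effective, power 80.4%.

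**Step 6. Dropout that breaks up pairs.** Step 4 keeps two completers per mentor. Suppose instead that each participant drops out independently, starting from 76/2 = 38 pairs per group:

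- Intact pairs: 38 × 0.75² = 21.4. They contribute 21.375 × 2/1.15 = 37.2 effective participants.
- Singles: 38 × 2 × 0.75 × 0.25 = 14.25, counted in full.
- Total effective number: 37.2 + 14.25 = 51.4, power 78.8%.

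The clustering factor is then 57/51.4 ≈ 1.11, and the number needed is 53 × 1.11/0.75 ≈ 78.4, or 79 per group.

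**Side scenarios, not needed for the point.**

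- At 27% attrition: 76 × 0.73/1.15 = 48.2 effective, power 76%.
- At 50% attrition: 76 × 0.50/1.15 = 33.0 effective, power about 60%.
- With unequal mentor caseloads, assuming a coefficient of variation of 0.5 (not in the document): factor 1 + 0.15 × [(1 + 0.25) × 2 − 1] = 1.225, effective number 57/1.225 = 46.5, power about 75%.

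**The case against.** - **The multiplication is inferred.** The article does not show the attrition step, and another route also reaches 76: with c = 1.5, the mean caseload left after 25% loss, 53 × 1.075/0.75 = 75.97. The first part stands, and the write-up should say that 76 is consistent with multiplying by 1.25. The alternative, however, contradicts the stated c = 2. Nor does 25% loss bring the factor down to 1.075: independent dropout gives about 1.11 (step 6). However 76 was obtained, 57 completers are fewer than 60.95.
- **77% is near the low end.** It keeps both members of each pair together. With independent loss, power is 78.8%. If all 80 planned volunteers serve, caseloads at entry average 152/80 = 1.9 and power is about 79%. This stands as to size: 77% to 79% is the fair range. It does not restore 80%.
- **Precision gains are ignored.** The mixed model includes the baseline value as a covariate, and withdrawn participants are invited back for assessment. If the 53 gives no credit for baseline adjustment, removing about 6.5% of residual variance (1 − 49.6/53; a correlation of about 0.25) would close the gap. That could happen, but the sample size section claims no such credit and itself budgets for 25% attrition.
- **The 27% to 50% range is selective.** It refers to other interventions of up to 12 months, whereas the primary analysis is at 6 months. The same paragraph of the Discussion cites 17% at 16 weeks in a peer-mentor trial. This is fair: the 25% is a defensible choice and not itself an error.

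**Conclusion.** The point holds. With the plan's own inputs, 76 per group covers 19.8% attrition. At the stated 25%, power is about 77% by the plan's own formula and about 79% if dropout is independent within mentor pairs. The correct inflation gives 82 per group (164 in total) instead of 76 (152), or 79 per group under independent dropout.

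The completer shortfall (57 against 60.95) follows from the printed figures with c = 2 and needs no further assumption. The power figures rest on the effect size implied by 53 per group at 80% power, on equal caseloads, and on no credit for baseline adjustment. The loss is about 1 to 3 percentage points. It is a wrong figure that should be corrected, but not a threat to the design.

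**What to change.** Restate the result and write out the formula. Either version is enough:

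- 76 per group gives 80% power, allowing for 20% attrition and a clustering factor of 1.15.
- 76 per group gives about 77% power at 25% attrition (about 79% if dropout is independent within mentor pairs); 53 × 1.15/0.75, or 82 per group, would be needed for 80%.

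It would help to add the power at 27% and 50% attrition (76% and about 60%), since the article cites that range itself, but the correction does not depend on it.

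The cost is one sentence and a slightly less favourable power statement; no further participants are needed. If recruitment is still open and 80% at 25% attrition is wanted, the alternative is 6 more per group, 12 in total.

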#### Data analysis

Continuous variables with normal distribution will be described using means and standard deviations; median and inter-quartile range will be used for those without a normal distribution. Categorical variables will be described using frequency tables. The efficacy of the intervention will be primarily assessed with an intention-to-treat (ITT) analysis at the end of the intervention with secondary analysis for the 12-month time point. This effect will be tested as the interaction between the allocation group (intervention and control) and time, on the primary and secondary outcomes. We will apply multilevel regression models (mixed models) with baseline value of each outcome included in the model as a covariate. In a complementary analysis, we will apply imputation by chained equations to perform an ITT analysis of primary and secondary outcome measures. Alpha will be set at 5% and all statistical tests reported will be two-tailed.

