The primary aim of this randomized controlled trial (RCT) among insufficiently active older adults at increased risk of developing AD is to determine whether a 6-month home-based physical activity (PA) intervention with individual goal-setting and peer mentors (GM-PA) leads to a significantly greater increase in PA compared to a the same PA program delivered with standard education and peer contact only (CO-PA). We hypothesize that participants randomized to the GM-PA intervention with peer mentors will show a significantly greater increase in their PA at the end of the intervention compared to participants randomized to the control group (CO-PA). A secondary aim is to determine if the GM-PA programs leads to better health outcomes compared to controls. Another secondary aim is to evaluate the health outcomes of peer volunteers.

The Melbourne Health Human Research Ethics Committee approved the study, the participants gave written consent to participate and the project complies with the Declaration of Helsinki.

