### Apolipoprotein (APOE) genotyping

As we and others have shown that the APOE genotype can interact with PA outcomes [12, 65] the APOE genotype will be adjusted for in the final analysis. A saliva sample for DNA will be collected at baseline using a Oragene DNA Self-Collection kit (Oragene DNA (OG-500) DNA Genotek Inc., Ontario, Canada). Determination of APOE genotype will be performed centrally at the Biochemistry Department at Royal Perth Hospital, Western Australia, using the method of Hixon and Vrernier (1990) [66]. All samples will be batched and processed once the final baseline assessment has been completed.

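### The stated primary test, group-by-time with baseline as a covariate, does not isolate the 6-month group difference that the trial is designed to test

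*Protocol article*

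**What the plan says.** The Background section hypothesises that participants given goal-setting and mentors "will show a significantly greater increase in their PA at the end of the intervention" compared with controls. The Data analysis section agrees on timing: efficacy is judged primarily at the end of the intervention, and 12 months is secondary. The sample size section is built on a difference between groups: "53 per group was estimated to give 80% power at α = 0.05 to detect a difference of 1200 steps/day".

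The Data analysis section then fixes the test: "This effect will be tested as the interaction between the allocation group (intervention and control) and time, on the primary and secondary outcomes". It specifies multilevel (mixed) models "with baseline value of each outcome included in the model as a covariate". Participants are assessed at baseline, 6 and 12 months (Follow-up assessments; Table 2). The text does not say whether the baseline measurement is also a row of the outcome, nor which term or contrast of the model gives the 6-month effect.

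**The concern.** In a repeated-measures model, what a group-by-time interaction means depends on which visits are in the outcome. With baseline among them, the interaction at 6 months is the difference in change from baseline. With baseline moved to the right-hand side, the only times left are 6 and 12 months. The interaction then asks whether the effect changed after the intervention ended, and the 6-month effect sits in a different term of the same model.

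The protocol names the interaction as the test and also puts baseline on the right-hand side. An analyst who follows it literally could report a null primary result for an effective and lasting intervention, or a positive one when nothing had happened by 6 months. Because the text supports more than one analysis, the choice of term could also be made after the data are seen.

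**Working it through.** **Inputs.** From the protocol article: 53 per group before inflation, 80% power and 1,200 steps/day (Sample size calculation); two-sided 5% level (Data analysis); visits at baseline, 6 and 12 months. Equal allocation is inferred from the equal group sizes. Not given, so assumed: the SD, the between-visit correlation ρ (0.5 and 0.7, equal for all pairs of visits), no dropout and no mentor clustering.

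**The plan's own figure.** The design effect is 1 + 0.15 × (2 − 1) = 1.15, and 53 × 1.15 × 1.25 = 76.2. This reproduces the stated 76 per group.

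**Implied SD.** From n = 2(1.960 + 0.842)²σ²/δ² with n = 53 and δ = 1,200, σ = 1,200 × √(53/2)/2.802 ≈ 2,205 steps/day. The protocol defines the outcome as change, so this may be the SD of change. Both possibilities are shown where it matters.

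**Case 1: baseline is a covariate only; outcome rows at 6 and 12 months.** Write D6 and D12 for the true group differences at the two visits. The interaction estimates D12 − D6. The baseline term is the same in both rows and cancels. This is algebra and needs no SD or correlation. With 2,205 as the SD at each visit, the standard error is 2,205 × √[2(1 − ρ)] × √(2/53), that is 428 at ρ = 0.5 and 332 at ρ = 0.7. For the baseline-adjusted contrast at 6 months it is 2,205 × √(1 − ρ²) × √(2/53), that is 371 and 306. Simulated rejection rates (8,000 trials per scenario; 4,000 for the last row):

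| True D6 / D12 | Mean interaction | Interaction significant (ρ = 0.5 / 0.7) | 6-month contrast significant (ρ = 0.5 / 0.7) |
|---|---|---|---|
| 1,200 / 1,200 | about 0 | 5% / 5% | 89–90% / 97% |
| 1,200 / 600 | about −600 | 30% / 44% | 89% / 97% |
| 0 / 1,200 | about 1,200 | 79% / 95% | 5% / 5% |

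A hand check agrees. For a true difference of 600, 600/428 = 1.40 gives 29% power, and 600/332 = 1.81 gives 44%.

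If 2,205 is instead the SD of change, the interaction's standard error is 428 at any ρ. The second row is then 29% and the third 80%. The 6-month contrast, with standard error 2,205 × √[(1 + ρ)/2] × √(2/53), has power of about 90% (ρ = 0.5) or 86% (ρ = 0.7). The first row stays at 5%.

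If only the 6-month visit is modelled, there is no time factor and no interaction to test.

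**Case 2: baseline is an outcome row and also a covariate.** The covariate again cancels, so the group-by-6-month term is the unadjusted difference in change. Its simulated mean is about 1,200 when D6 = 1,200, so the target is right.

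- *Rows at 0 and 6 months, random intercept.* The pooled slope on baseline is (1 + ρ)/2, which leaves negatively correlated residuals within a person. The random-intercept variance is therefore estimated as zero in almost every run. The ratio of model variance to true variance is 0.75 + 0.25ρ: 0.85, 0.875 and 0.925 at ρ = 0.4, 0.5 and 0.7. The actual type I error is 2[1 − Φ(1.96 × √ratio)] = 7.1%, 6.7% and 5.9%. Simulation gave 6.8% at ρ = 0.5 and 6.1% at ρ = 0.7.
- *Rows at 0, 6 and 12 months, random intercept.* Simulated type I error was 5.0–5.5%. Power was 80% against 89% for the baseline-adjusted contrast at ρ = 0.5, and 95% against 97% at ρ = 0.7.
- *Joint interaction test over all three visits.* This has 2 degrees of freedom and mixes the 6- and 12-month effects, so it is again not the 6-month test.

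**The case against.** The best defence is context. The sentence just before the one that names the interaction puts efficacy at the end of the intervention, and the outcome is defined as change. On that view, group-by-time is the familiar shorthand for a difference in change from baseline, and nobody intends a comparison of 6 with 12 months. Even with baseline only as a covariate, the fitted model contains the 6-month group effect. Row layout, time coding and contrast statements are often left to a statistical analysis plan, which is not shown.

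Part of this stands. The intended question is clear, and the model family can answer it. But the article did not leave the test open: it named a term and a covariate, and on the plain reading of a covariate that term is the wrong one. Defining the outcome as change does not rescue it either, because change at baseline is zero for everyone and so supplies no usable baseline row.

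Two stronger readings should not be drawn. A reader might infer that the test is invalid whichever way baseline is handled. It is not: with baseline as an outcome row the 6-month term is unbiased, and the inflated error belongs to the two-visit random-intercept fit and was not seen with three visits. A reader might also see a second, conflicting primary model in the genotyping section, where "the APOE genotype will be adjusted for in the final analysis". The Data analysis section does not claim a complete covariate list, so the two can be read as complementary. Nothing in the document supports telling the sponsor to exclude APOE.

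**Conclusion.** Wrong as written, and correctable by wording. The protocol names as its primary test a term that, with baseline as a covariate only, measures how the effect changes between 6 and 12 months. That a sustained benefit then gives an expected interaction of zero, and so about a 5% chance of significance, follows from the algebra and from no assumed figure. With baseline also an outcome row, the fault is smaller: a redundant covariate, lost precision (for example 80% against 89% power at a correlation of 0.5), and type I error of about 6–7% at correlations of 0.4–0.7 in a two-visit random-intercept fit only.

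The other power and error figures rest on the back-solved SD, equal correlations between visits, complete data and no clustering by mentor. They show the scale of the problem and are not forecasts for this trial.

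**What to change.** State one primary model and name the contrast. Either of these would do:

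1. Outcome rows at 24 and 48 weeks; fixed effects for group, visit (categorical), group-by-visit and baseline steps, optionally with baseline-by-visit. The primary test is the GM-PA minus CO-PA difference at 24 weeks. The 48-week difference is secondary.
2. Baseline kept as an outcome row and removed as a covariate. The primary test is the group-by-24-week term.

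In both, say that the omnibus interaction is not the primary test. The cost is a few sentences in the protocol or analysis plan and a few lines of code, with no new data and no change to the sample size.

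### The primary mixed model and the complementary chained-equation imputation share the missing-at-random assumption, so their agreement is no check on it for participants who withdraw and are not measured again

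*Protocol article*

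**What the plan says.** All references are to the protocol article.

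- **Outcome** (Sample size calculation): "The primary outcome will be the change in PA at follow-up as measured by the pedometer in steps/day".
- **Primary question** (Data analysis): efficacy is "primarily assessed with an intention-to-treat (ITT) analysis at the end of the intervention with secondary analysis for the 12-month time point".
- **Test** (Data analysis): "This effect will be tested as the interaction between the allocation group (intervention and control) and time". The model is a mixed model "with baseline value of each outcome included in the model as a covariate".
- **Complementary analysis** (Data analysis): "In a complementary analysis, we will apply imputation by chained equations to perform an ITT analysis of primary and secondary outcome measures". The article states no missingness assumption and no predictors for the imputation.
- **Retrieval** (Statistical analysis): "Participants who withdraw during the trial will be invited to return for the follow-up assessments to allow for an intention-to-treat analysis".
- **Expected loss** (Sample size calculation): "we have accounted for a potential 25% attrition rate". The Discussion cites 27% to 50% in earlier physical activity interventions in older adults, "with most of the attrition occurring in the first 3 months". The first outcome visit is at 24 weeks (Table 2).

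**The concern.** The ITT question is about steps/day in everyone randomised, including those who leave. For a participant with no follow-up pedometer week, the mixed model relies on MAR: given what was observed, the missing steps look like those of comparable measured people. Chained-equation imputation in its usual form relies on the same assumption and fills the gap from measured people. The complementary analysis therefore cannot show whether the primary result depends on MAR.

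This matters more here than in many trials. The outcome is the behaviour that a person who leaves an activity program may well have stopped, so absence of a value and a low value are plausibly linked. If so, a figure near the 1200-step benchmark could be reported from two seemingly concordant analyses while the effect in the randomised population is different.

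**Working it through.** **1. The plan's own figures.** The base sample is 53 per group, for 1200 steps/day at 80% power and two-sided 5%. No SD is given; solving back gives about 2205. The design effect is 1 + 0.15 x (2 - 1) = 1.15. Then 53 x 1.15 x 1.25 = 76.2, which reproduces 76 per group. The 25% enters as an allowance for lost sample.

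**2. Assumptions not in the documents.** Among those retained, the control gain is g and the GM-PA gain is g + 1200. Unretrieved quitters have zero change from baseline. Unretrieved loss is d_GM and d_CO. The article gives 1200 as the difference to detect, not as an effect in those retained.

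**3. Effect in all randomised.**

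ITT effect = (1 - d_GM)(g + 1200) - (1 - d_CO) g

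An analysis under MAR, using arm and baseline, estimates about 1200. Subtracting:

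Overstatement = 1200 d_GM - g (d_CO - d_GM)

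**4. Equal loss, nobody retrieved** (g cancels).

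| Loss per arm | ITT effect | Estimate | Gap |
|---|---|---|---|
| 10% | 0.90 x 1200 = 1080 | 1200 | 120 |
| 25% | 0.75 x 1200 = 900 | 1200 | 300 |
| 50% | 0.50 x 1200 = 600 | 1200 | 600 |

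**5. Equal 25% loss, share r of withdrawals retrieved**, each measured at zero change. The estimate is (0.75 x 1200)/(0.75 + 0.25 r), against an ITT effect of 900.

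| r | Estimate | Gap |
|---|---|---|
| 0 | 1200 | 300 |
| 0.25 | 1108 | 208 |
| 0.50 | 1029 | 129 |
| 0.75 | 960 | 60 |
| 1 | 900 | 0 |

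**6. Unequal loss, nobody retrieved.** The sign changes when d_CO/d_GM exceeds 1 + 1200/g, which is 2.2, 1.8 and 1.6 for g = 1000, 1500 and 2000.

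| GM-PA / CO-PA loss | g | ITT effect | Estimate minus ITT |
|---|---|---|---|
| 30% / 20% | 1500 | 0.70 x 2700 - 0.80 x 1500 = 690 | +510 |
| 20% / 30% | 1500 | 0.80 x 2700 - 0.70 x 1500 = 1110 | +90 |
| 15% / 35% | 1500 | 0.85 x 2700 - 0.65 x 1500 = 1320 | -120 |
| 35% / 15% | 2000 | 0.65 x 3200 - 0.85 x 2000 = 380 | +820 |
| 15% / 35% | 2000 | 0.85 x 3200 - 0.65 x 2000 = 1420 | -220 |

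**7. Do the two methods really move together?** A large simulation (400,000 participants, g = 1000 except where stated) compared the full-data effect, the baseline-adjusted analysis of measured participants, and MAR imputation from arm and baseline.

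| Loss GM-PA / CO-PA, retrieval | Full data | Measured only | MAR imputation |
|---|---|---|---|
| 25% / 25%, none | 893 | 1193 | 1194 |
| 25% / 25%, half (g = 0) | 899 | 1029 | 1033 |
| 35% / 15%, none | 592 | 1207 | 1208 |
| 15% / 35%, none | 1219 | 1203 | 1204 |

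A separate simulation with 76 per arm, 25% loss and g = 1500 gave 903, 1207 and 1204. In every scenario run the two methods differed by at most 4 steps/day, however far both lay from the full-data value. The simulations used one follow-up visit and ignored clustering by mentor. They test whether the methods agree with each other; they do not predict this trial's result.

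**The case against.** **Imputation detail belongs in the SAP.** The article gives one sentence on imputation, and the SAP is not at hand. Chained equations could include diary minutes, CHAMPS scores and withdrawal status, which would make MAR more plausible. This stands as far as missing detail goes: the absence of predictors or of a sensitivity analysis is not in itself a fault. The article does, however, choose the complementary method itself and label it ITT. In its ordinary form that method shares the primary model's assumption.

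**Withdrawals are invited back.** This stands and limits the size. Anyone who stops the program but is measured enters with the steps actually taken. A reader might infer that both analyses answer what would have happened had nobody quit. The document does not support that: only people who leave and are not measured are modelled. Likewise, the Background figure of 50% giving up an exercise program by six months concerns stopping exercise, not missing pedometer data.

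**Participants with no follow-up may not be dropped.** A reader might infer from the baseline covariate that they are. The wording leaves this open. A group-by-time interaction with only 6- and 12-month rows would compare the effect at those two visits, so baseline may also be an outcome row. The analysis would still assume MAR on either reading.

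**The direction is not fixed.** This stands too. Both arms receive the same activity program, so control quitters also lose their gain. A reader might infer that the effect will be overstated. That does not follow without knowing loss by arm, retrieval, and what unmeasured quitters do.

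**Conclusion.** The concern holds in a limited form. The two named analyses, as ordinarily run, rest on one assumption, so their agreement is not evidence of robustness to informative withdrawal.

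The size is conditional on zero change in unretrieved quitters and 1200 steps/day in those retained. With 25% unretrieved loss in each arm the gap is 300 steps/day, a quarter of the plan's benchmark. It falls to about 129 if half of the withdrawals return and to nothing if all do. Over the loss patterns examined without retrieval, the estimate minus the ITT effect ran from +820 to -220 steps/day. The document establishes neither the sign nor the size of any bias, but the analyses it names would not reveal either. The change is worth making; the primary model does not need replacing.

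**What to change.** Keep the mixed model as the primary analysis. Make the complementary imputation, or one added beside it, a departure-from-MAR analysis of 6-month steps/day:

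- Unretrieved withdrawals in both arms are imputed from their own baseline steps plus residual variation, with no arm-specific gain.
- Where enough withdrawals return, impute instead from those returned values, with arm, withdrawal status and diary minutes in the imputation model.
- Report this estimate beside the primary one, with the numbers lost and retrieved in each arm.

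It should not be a condition for claiming benefit: return to baseline is itself untestable, and a gate would cost power. A split by reason for missingness is best avoided, since the article does not say that reasons are collected.

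No new data are needed. Baseline pedometer steps and monthly diaries are already planned, and inviting withdrawals back requires knowing who withdrew. The cost is a little more analysis work, and this estimate may be smaller and less precise than the primary one.
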